### Study design and setting

This study will be a two-arm non-randomized (observational) multicenter cohort study and an economic evaluation alongside. The study will be conducted with a non-inferior design. Relevant societies for surgery (Dutch Association of Surgery (NVvH), Dutch Association of Trauma Surgery (NVT), Dutch Orthopaedic Association (NOV), and Dutch Association of Orthopaedic Surgery (NVOT)), clinical geriatrics (Dutch Association of Clinical Geriatrics (NVKG)), elderly care (Association of Elderly Care Physicians (VERENSO)), the Dutch Patient Federation, and two committee members of the Dutch guideline for treatment of proximal femoral fractures are represented in the study team. Patients will be recruited from several hospitals throughout The Netherlands. The following 26 hospitals will participate: Albert Schweitzer Ziekenhuis, Alrijne Ziekenhuis, Amphia Ziekenhuis, Amsterdam UMC (location VUmc), Bernhoven, Catharina Ziekenhuis, Deventer Ziekenhuis, Dijklander Ziekenhuis (location Westfriesgasthuis), Dijklander Ziekenhuis (location Waterland Ziekenhuis), Elisabeth TweeSteden Ziekenhuis, Erasmus MC, Flevo Ziekenhuis, Isala, Maasstad Ziekenhuis, Meander MC, Noordwest Ziekenhuisgroep, OLVG, Radboud UMC, Rijnstate, Rode Kruis Ziekenhuis, St. Antonius Ziekenhuis, Streekziekenhuis Koningin Beatrix, Tergooi, Ziekenhuis Gelderse Vallei, Ziekenhuis Tjongerschans, and Zorggroep Twente.

The study has started in September 2018. The recruitment period will be 24 months, with a follow-up of 6 months. The results of the study are expected mid-2021.

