### Treatment of participants

#### Shared decision process

The decision for type of treatment (operative or nonoperative) is achieved by shared decision making (SDM). Shared decision making is based on determining the goals of care for the patient [27]. The purpose of goals of care is to safeguard patients who are unlikely to benefit from operative treatment, especially in patients in the palliative or terminal phase. Goals of care discussion with these frail elderly patients, or in case of cognitive impairment, with a proxy at the onset of proximal femoral fracture are useful in shared decision making. Although some form of SDM is also used in current practice, this study will use a much more structured approach towards this process. Prior to start of treatment, patients will be informed in an objective and structured way about what either treatment arm of the study involves and what complications may occur in either treatment arm. Both for nonoperative and operative management, a full forecast is given verbally and on paper. Combined with the preferences and objections of the patients or their proxy, this is the starting point of a shared decision process. All principal health care providers (i.e., a trauma or orthopedic surgeon, elderly care physician, and geriatrician if possible) as well as the patient and his/her relative(s) or legal representative will take part in this shared decision process. The patients perspective will play a key role in the decision process.

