### Study procedures and follow-up

Patients will be followed until 6 months after trauma or until death, whichever comes first. In addition, at the 6-month follow-up contact, the researcher or research assistant will document any secondary intervention that may be planned for the patient. A schedule of events is shown in Table 1. A flow chart is shown in Fig. 1.

**Table 1 Tab1:** Schedule of events and follow-up

Radiographs & Event forms	Screening	Enrolment	7 days (4–10 days)	14 days (11–17 days)	30 days (23–37 days)	3 months (11–15 weeks)	6 months (6–7 months)
X-ray or CT-scan	X						
Screening	X						
Informed Consent		X					
Shared Decision		X					
Baseline Data			X				
General Clinical FU			X	X	X	X	X
QoL (EQ-5D and QUALIDEM)			X^a^	X	X	X	X
PACSLAC and Analgesic use			X^a^	X	X	X	X
Complications and mortality			X	X	X	X	X
(Secondary) Interventions			X	X	X	X	X
Satisfaction of patient (or proxy)			X^b^	X^b^	X^b^	X^b^	X
QODD			X^b^	X^b^	X^b^	X^b^	X^b^
Satisfaction of caregiver			X^b^	X^b^	X^b^	X^b^	X
Health Care Use			X^a^	X	X	X	X
Early Withdrawal			^c^	^c^	^c^	^c^	^c^

EQ-5D is completed by proxy and (if possible) by patients themselves

^a^Asking for current and pre-trauma status; ^b^Only if patients died prior to that follow-up moment; ^c^Only if applicable

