### Statistical analysis

Data will be analyzed using the Statistical Package for the Social Sciences (SPSS) version 24.0 or higher (SPSS, Chicago, Ill., USA) and will be reported following the STrengthening the Reporting of OBservational studies in Epidemiology (STROBE) guidelines. Normality of continuous data will be tested with the Shapiro-Wilk test. Homogeneity of variances will be tested using the Levene’s test. A two-sided *p*-value < 0.05 will be taken as threshold of statistical significance in all statistical tests. The analysis will be performed on a per-protocol basis, (as that is the most conservative approach) and verified by an intention-to-treat analysis if needed. Patients who have died will remain in the analysis as censored. If necessary, missing values will be replaced using multiple imputation following the predictive mean matching method, using ten imputations.

Descriptive analysis will be performed in order to report the outcome measures and other variables collected for the entire population as well as per treatment group. Continuous data will be reported as mean and SD (if Normal) or median and quartiles (if non-Normal), categorical data as number with percentage.

Univariate comparison between the groups will be done using Student’s T or Mann-Whitney U-test (for Normal and non-Normal data, respectively), or Chi-squared test or Fisher’s Exact test (categorical data, as applicable). The Student’s T-test will be done with equal variance assumed or not assumed, based upon the results of the Levene’s test.

For the primary outcome measure, a non-inferiority margin of 0.15 points for mean EQ-5D scores was chosen because it is reasonable and on the border of what would be considered a clinically important effect. The null hypothesis in the non-inferiority framework is that nonoperative management is inferior to operative management with regards to the EQ-5D score. This hypothesis will be tested through the adjusted contrast between the two interventions at 6 months. Specifically, the 95% confidence interval of the estimated contrast will be examined, and if the limit of the interval is less than the threshold value of 0.15 points, non-inferiority of nonoperative management to operative management at 6 months will be concluded.

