Multivariable analysis for continuous outcome measures that are repeatedly measured over time will be done using generalized estimating equations (GEE) for longitudinal analysis on a per-protocol and intention-to-treat basis to investigate the effect of treatment. In the primary GEE model, the primary outcome variable studied (quality of life on EQ-5D) will be analyzed as a dependent variable, using treatment (nonoperative versus operative) as between subjects variable and time as within subjects variable. The interaction term of group and time (group x time) will be assessed, to evaluate whether the change over time differed between groups. Analyses will be corrected for baseline differences and all models will be corrected for center of inclusion. Repeatedly measured continuous secondary outcome variables will be analyzed using similar GEE models. Continuous outcome measures only ones and dichotomous secondary outcome measures will be analyzed using multivariable linear regression models and logistic regression models, respectively.

Subgroup analysis are planned for patients with an intracapsular or extracapsular fracture.

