The economic evaluations will be done from a societal perspective. Intervention costs and health care utilization costs until 6 months after inclusion will be measured in accordance with economic guidelines [45]. Cost prices of the standardized referral strategy will be determined by bottom-up micro-costing method. The economic evaluation will be performed in accordance with the intention-to-treat principle. Missing data will be imputed using multiple imputation by changed equations [46]. The Incremental Cost-Effectiveness Ratio (ICER) of nonoperative versus operative management will be calculated by dividing the difference in costs by difference in effects. A cost-utility analysis, with QALY (based on the EQ-5D utility score) as outcome measure, will be done as primary economic analysis. As secondary analysis, a cost-effectiveness analysis, with QUALIDEM as outcome measure, will be done. In order to account for the possible clustering of data, analyses will be performed using linear multilevel analyses [47]. Accounting for the possible clustering of data (e.g., at the hospital level) is very important, as most economic evaluations fail to do so, whereas ignoring the possible clustering of data might lead to inaccurate levels of uncertainty and inaccurate point estimates [47]. Bootstrapping techniques will be used in order to estimate the uncertainty surrounding the cost-effectiveness estimates. Uncertainty will be shown in cost-effectiveness planes and cost-effectiveness acceptability curves, and sensitivity analyses will be performed in order to test the robustness of the study results [48–50].

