## Discussion

Treatment guidelines for proximal femoral fractures are mainly focused on regaining function and independence in activities of daily living. Other considerations may apply to frail elderly with a limited life expectancy, for whom comfort and pain are particularly relevant. Whether or not operative treatment is needed in this respect is undecided. This study aims to investigate the value of nonoperative management versus operative management of proximal femoral fractures in a selected group of frail institutionalized elderly with a limited life expectancy.

There are some limitations to this study. First, selection bias could be a factor in this study, since patient or proxy opting for nonoperative management may arguably be in worse condition with regards to their pre-trauma condition and comorbidities. A randomized controlled trial (RCT) would have avoided selection bias, however randomizing patients with a limited life expectancy was considered unfeasible (and unethical) by the research team. Patient recruitment in trials randomizing between operative and nonoperative treatment is known to be challenging, and would likely introduce an unacceptably high level of selection bias; surgeons with clear preference for a particular treatment may be unwilling to inform patients about the study, and patients (or their proxy if patient is unable to decide) with preference for a particular treatment will not sign informed consent. The chosen observational design allows all centers and all patients to participate, and real-life data will be collected. For patients with severe cognitive impairment, informed consent will be obtained by their health care proxy. That makes the current study design the most feasible to investigate this issue. As a second limitation, it could be argued that the questionnaire completed by proxy may differ from the patients rating, however since the majority of this study population is expected to suffer from cognitive impairment, questionnaire completion by proxy will be inevitable. Finally, at least 26 hospitals will participate, and treatment protocol and shared decision processes may vary across sites. This may introduce some heterogeneity, but also makes the results more generalizable.

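### In a non-randomised comparison, adjustment is tied to observed baseline differences rather than to a fixed prognostic set, so real confounders can be left out and pre-trauma EQ-5D is not assured a place in the primary model

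*Protocol article*

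**What the plan says.** The protocol article, under Study design and setting, describes the design thus: "This study will be a two-arm non-randomized (observational) multicenter cohort study and an economic evaluation alongside". Treatment follows from a structured shared decision. The Discussion names the resulting threat: "patient or proxy opting for nonoperative management may arguably be in worse condition with regards to their pre-trauma condition and comorbidities".

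Under Statistical analysis, the primary conclusion rests on an adjusted 6-month contrast in EQ-5D, whose 95% confidence limit is compared with 0.15. The primary GEE model has treatment, time and their interaction. The rule for further covariates is one sentence: "Analyses will be corrected for baseline differences and all models will be corrected for center of inclusion".

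Other study parameters says that the baseline variables are gathered to judge whether the groups are similar. Patient characteristics lists age, BMI, ASA grade, Charlson index, FAC and KATZ-ADL, among others. Injury characteristics adds fracture type. Pre-trauma EQ-5D is in neither list. It appears only through a footnote to the day-7 column of Table 1: "Asking for current and pre-trauma status".

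**The concern.** With no randomisation, adjustment carries the whole inference. What makes a covariate worth adjusting for is that it affects both the treatment choice and later EQ-5D. Whether it happens to differ visibly in this sample is a poor stand-in. A strong predictor with a moderate imbalance can pass as balanced and still move the contrast, while a weak predictor with a large imbalance is adjusted for to little purpose. The choice is also made after the data are seen.

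Pre-trauma EQ-5D is the baseline value of the primary outcome and so an obvious candidate. Under the stated rule it enters only if the groups are judged to differ on it. One could read the sentence as correction for baseline values of the outcome. Pre-trauma EQ-5D would then enter, but nothing would be said about the other confounders. Neither reading secures both.

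At stake is the non-inferiority conclusion. If nonoperative patients are frailer, as the Discussion expects, an omitted confounder makes nonoperative care look worse than it is. An imbalance the other way would flatter it.

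**Working it through.** **Inputs from the article.** SD of EQ-5D 0.30, margin 0.15, 160 to be recruited (Sample size calculation); threshold for all tests two-sided 0.05 (Statistical analysis). The stated equivalence of the margin to half an SD reproduces: 0.15 / 0.30 = 0.5. The article gives no figure for the effect of adjustment, so there is nothing further to reproduce.

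**Assumptions.** Differences judged by a t-test at 0.05; equal arms of 80 (allocation is not controlled); true imbalance d of 0.3 to 0.5 SD; within-arm correlation r of 0.3 to 0.7 between covariate and follow-up EQ-5D; omitted covariate unrelated to those adjusted for.

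**Step 1: chance that an imbalance is flagged.** The noncentrality is d × √(n₁n₂/(n₁+n₂)) = d × √40 = 6.32d, and the critical value on 158 df is 1.975.

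| True imbalance | Noncentrality | Flagged | Missed |
|---|---|---|---|
| 0.3 SD | 1.90 | 47% | 53% |
| 0.4 SD | 2.53 | 71% | 29% |
| 0.5 SD | 3.16 | 88% | 12% |

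Unequal arms lower these chances. The Background reports 20.3% treated nonoperatively in the literature review. A split of 32 to 128 would give √(32 × 128/160) = 5.06 in place of 6.32, and flagging chances of 33%, 52% and 71%.

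**Step 2: bias if the covariate is left out.** Bias = d × r × 0.30. Percentages are of the 0.15 margin.

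| | r = 0.3 | r = 0.5 | r = 0.7 |
|---|---|---|---|
| d = 0.3 | 0.027 (18%) | 0.045 (30%) | 0.063 (42%) |
| d = 0.4 | 0.036 (24%) | 0.060 (40%) | 0.084 (56%) |
| d = 0.5 | 0.045 (30%) | 0.075 (50%) | 0.105 (70%) |

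**Step 3: how the two steps fit together.** Within one sample, the bias depends on the observed imbalance. With 80 per arm, a difference that escapes the 0.05 test must be below 1.975 × √(2/80) = 0.31 SD. A single unflagged covariate then biases the contrast by at most 0.31 × 0.7 × 0.30 = 0.066, or 44% of the margin. At 32 to 128 the limit is 1.975/5.06 = 0.39 SD, giving 0.39 × 0.7 × 0.30 = 0.082, or 55%. The top of the table therefore needs a looser way of judging difference than this test, a more uneven split, or several omitted covariates acting together.

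**The case against.** **The article does not say that p-values choose the covariates.** This is right. It plans group comparisons ("Univariate comparison between the groups will be done using Student’s T or Mann-Whitney U-test") but never links them to the choice of covariates. A reader might infer selection by significance. The flagging percentages rest on that reading and illustrate the problem only. The objection to the rule does not depend on it: any criterion based on observed difference ignores prognostic weight.

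**A covariate list may sit in an analysis plan that is not shown.** This is possible, and a missing list is not the point. The point is the rule that is stated: a plan faithful to it inherits a choice driven by the data.

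**A large imbalance in a strong confounder would usually be noticed.** This also stands. At 80 per arm, 0.5 SD is flagged 88% of the time, so the rule can miss confounders but will not always do so. Using 32 per arm, which gives 35% for 0.4 SD, would be wrong: listed baseline characteristics can be compared in all 160 enrolled, not only in those left after attrition.

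**A reader might go further and say that centre adjustment consumes the information.** The article states "The following 26 hospitals will participate" and corrects all models for centre. However, it does not say how centre is coded, so 25 indicators is an inference. Even with that coding, simulation of the planned five-visit GEE with 160 enrolled (assumed retention and within-patient correlation) inflates the standard error of the 6-month contrast by only about 3% to 12%, with about 20% to 28% of centres having one arm only. Inflation of 25% to 39%, and half the centres with one arm, come from a cross-section of 160 × 0.4 = 64 patients, which is not the planned analysis. No calculation shows that the logistic models would fail, and deaths are events there, not losses. The economic evaluation does use multilevel models, but fixed against random centre effects is a trade-off: a random intercept removes between-centre confounding less fully.

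**A reader might also want pre-trauma EQ-5D asked at enrolment.** The gain is small. Patients who die before the day-7 visit have no follow-up EQ-5D either, and the answer is recalled after trauma in both cases.

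**Conclusion.** The concern holds for the confounder rule and should be acted on; it does not extend to centre. In a study with acknowledged confounding by indication, adjustment keyed to observed imbalance can omit covariates that matter and does not ensure the use of pre-trauma EQ-5D. The possible bias from one omitted covariate is about 0.03 to 0.11, or 18% to 70% of the margin, over the assumed ranges of imbalance and correlation. If selection were by a 0.05 test in equal arms of 80, the single-covariate ceiling is about 0.066, or 44%. Only the SD, the margin, the recruitment target and the 0.05 threshold come from the article. The imbalance, the correlation, the arm sizes and the use of the test for selection are assumptions. The figures show that the choice of covariates could decide the result, not that it will.

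**What to change.** In Statistical analysis, replace the correction for baseline differences with adjustment for a fixed set chosen on prognostic grounds and applied whatever the observed balance: pre-trauma EQ-5D, age, ASA grade, Charlson index, KATZ-ADL, FAC, BMI and fracture type. Where events are few, as in some of the logistic models, enter the set through a propensity score. The correction for centre can stay.

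The cost is small. Every variable is already collected, and the change is one sentence. The models gain a few terms, and any missing covariate values fall under the multiple imputation already planned. One weakness remains and should be stated: pre-trauma EQ-5D is recalled at day 7, after treatment has been chosen, so the answer may be coloured by it.

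### The economic paragraph corrects for hospital clustering but does not clearly say that incremental costs and effects are adjusted for baseline differences, although treatment is not randomised and pre-trauma values are collected

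*Protocol article*

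**What the plan says.** Study design and setting describes a "two-arm non-randomized (observational) multicenter cohort study and an economic evaluation alongside". Under Shared decision process, the treatment arm follows from a discussion between patient or proxy and care providers.

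The economic paragraph of Statistical analysis sets its own methods: intention-to-treat, multiple imputation, an ICER that "will be calculated by dividing the difference in costs by difference in effects", bootstrapping, planes and acceptability curves. On the model it says: "In order to account for the possible clustering of data, analyses will be performed using linear multilevel analyses". A further sentence stresses how important clustering is. The paragraph also promises that "sensitivity analyses will be performed in order to test the robustness of the study results", without saying which. It mentions neither covariates nor confounding.

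The preceding paragraphs, on the GEE and regression models, contain the only statement on baseline adjustment: "Analyses will be corrected for baseline differences and all models will be corrected for center of inclusion".

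Table 1 in Study procedures and follow-up marks EQ-5D, QUALIDEM and health care use at the 7-day visit with the footnote "Asking for current and pre-trauma status".

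The Discussion names selection bias as the first limitation: "patient or proxy opting for nonoperative management may arguably be in worse condition with regards to their pre-trauma condition and comorbidities".

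**The concern.** A cost-utility comparison in a non-randomised cohort needs adjustment for prognosis as much as the clinical comparison does. If nonoperative patients start in worse health, they accumulate fewer QALYs whatever the treatment does. Their costs may differ for the same reason. The document's own literature review notes that mortality depends on comorbidity, and death ends the accrual of both QALYs and costs.

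None of the tools named in the economic paragraph removes this. A multilevel model without patient covariates handles dependence within hospitals. The bootstrap describes the spread around whatever is estimated. Intention-to-treat does not balance groups that were never randomised.

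An analyst who took the paragraph literally could produce planes and acceptability curves centred on a confounded estimate. The clinical analysis of the same EQ-5D data would be adjusted and the economic one not, so the two could point in different directions. The Discussion says that the results may feed into national guidelines.

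**Working it through.** The document states no cost, QALY or ICER figure, so there is nothing to reproduce. The check is a comparison of the texts, followed by an illustration.

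**1. Does the baseline-correction sentence reach the economic models?** Both texts stand under Statistical analysis in the Protocol article.

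| Feature | Clinical analyses | Economic evaluation |
|---|---|---|
| Population | per-protocol, verified by intention-to-treat | intention-to-treat |
| Imputation | predictive mean matching, ten imputations | described separately, with its own reference |
| Model | GEE, linear or logistic regression | linear multilevel |
| Hospital | corrected for centre | multilevel, for clustering |
| Treatment effect | an adjusted contrast | a difference in costs and a difference in effects |
| Baseline differences | corrected for | not mentioned |

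The economic paragraph restates or replaces every other feature and does not refer back. It deals with hospital afresh, which would be largely unnecessary if the GEE paragraph already governed it. The reach of the baseline sentence is therefore doubtful, but it is not excluded.

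**2. Are the covariates available?** Yes. Table 1 collects pre-trauma values for all three economic outcomes: EQ-5D for QALYs, QUALIDEM for the secondary effect and health care use for costs. Patient characteristics lists age, ASA, CCI, FAC and KATZ-ADL. Injury characteristics lists fracture type.

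**3. How large could the shift in QALYs be?** Inputs: a horizon of 0.5 year (six months, from the economic paragraph), an assumed pre-trauma utility gap, and an assumed share of that gap that persists through follow-up. Deaths are ignored.

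Spurious QALY difference = 0.5 × gap × share persisting.

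| Assumed gap | Half persists | All persists |
|---|---|---|
| 0.05 | 0.5 × 0.05 × 0.5 = 0.0125 | 0.5 × 0.05 × 1 = 0.025 |
| 0.10 | 0.5 × 0.10 × 0.5 = 0.025 | 0.5 × 0.10 × 1 = 0.050 |
| 0.15 | 0.5 × 0.15 × 0.5 = 0.0375 | 0.5 × 0.15 × 1 = 0.075 |

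**4. What would that do to the ratio?** Assume a cost difference of −10,000 and a true QALY difference of −0.05, so the true ratio is −10,000 / −0.05 = 200,000 per QALY. Hold costs fixed and let the gap persist fully:

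- gap 0.05: −10,000 / −(0.05 + 0.025) ≈ 133,000
- gap 0.10: −10,000 / −(0.05 + 0.050) = 100,000
- gap 0.15: −10,000 / −(0.05 + 0.075) = 80,000

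These figures show only how sensitive the ratio is. Confounding of costs would move it further, in a direction that the document does not allow one to fix.

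**The case against.** The strongest reply is that the document nowhere specifies an unadjusted ICER. A ratio of two differences is the definition of an ICER in any design and is compatible with adjusted differences. A linear multilevel model can carry covariates. The baseline-correction sentence is worded generally, stands under the same heading and can be read to cover the economic models; multilevel modelling is one way of correcting for centre, so the two texts do not conflict. A condensed article may leave covariate lists to the full protocol or a health-economic plan, and the unspecified sensitivity analyses might include adjustment.

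Most of this stands. A reader might infer that the plan has chosen a crude comparison and that its cost per QALY is therefore confounded. The text does not support that, because silence about covariates is not a decision against them. The absence of a covariate list is not itself a fault either.

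What remains is narrower. The paragraph gives the economic evaluation its own methods, singles out clustering as what must be accounted for, and leaves it unclear whether the adjustment promised for the clinical analyses applies. The selection bias that the authors list first among their limitations is not addressed there.

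A reader might also convert the 0.15 EQ-5D limit to a QALY margin and judge power or precision against it. That would not be sound. No non-inferiority test on QALYs is planned. The 50 per arm in Sample size calculation is the clinical target before allowance for loss and mortality, not the intention-to-treat economic sample (about 80 per arm if the 160 split evenly). The document gives no SD for QALYs.

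**Conclusion.** The point holds as an ambiguity with real consequences: the economic paragraph names correction for hospital clustering only, and the baseline-correction sentence does not clearly extend to it. Followed as written, the ICER is at risk of confounding in both numerator and denominator. It should be settled before analysis.

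The size is unknown. Under the assumed gaps of 0.05 to 0.15, the spurious difference is 0.0125 to 0.0375 QALY at half persistence and 0.025 to 0.075 at full persistence. This leaves out any effect through mortality or costs. The qualitative conclusion rests on the documents: non-randomised design, choice by shared decision, and imbalance expected by the authors. The figures rest on assumptions, and no claim is made about power or non-inferiority on QALYs.

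**What to change.** In the economic paragraph, state that the incremental costs and effects in the ICER are the adjusted treatment coefficients from the linear multilevel models already planned, with these covariates:

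- pre-trauma EQ-5D utility in the QALY model;
- pre-trauma QUALIDEM in the QUALIDEM model;
- pre-trauma health care use in the cost model;
- in all three, the same already-collected prognostic factors as in the clinical models (candidates are age, ASA, CCI, FAC, KATZ-ADL and fracture type).

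State that the bootstrap is run on these adjusted models, so that the planes and acceptability curves show adjusted estimates. The crude ICER may be shown alongside. If a fuller plan already provides for this, one sentence of cross-reference is enough.

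The cost is a wording change and a few covariates, with no new data, visits or patients. One small downside: pre-trauma values are asked for at the 7-day visit and will be missing for some early deaths, so they must enter the imputation already planned. Adjustment removes only measured imbalance, so residual confounding should still be acknowledged.
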